##### Physical Fitness

Balance

The tests will be performed on a Kistler force platform (Type 9286a, Kistler Instrumente AG, Winterthur, Switzerland), and the signal recording will be set at 200 Hz [67]. The sway area in cm², the mean amplitude from RMS (root mean square), and the mean velocity in the anteroposterior and mediolateral directions in cm/s will be recorded. In addition, the entropy (SampEn) in the anteroposterior and mediolateral directions will be obtained to determine the regularity with which the COP trajectory repeats [20,67].

Different static posturography tests will be performed to analyze the center of pressure (COP) pattern as well as to establish a sensory analysis of the visual, proprioceptive, and vestibular systems. The tests will be performed in a static position with eyes open (EO) and static position with eyes closed (EC). Each test will have a duration of 45 s [68], where the first 5 s will be considered as adjustment time before starting the recording [69].

Strength 

This test will be performed on the isokinetic dynamometer (Multi-Joint 3, Biodex Medical Systems, Inc., Shirley, NY, USA).

Isokinetic dynamometry (ID) allows for the measurement of the strength of the agonist and antagonist muscles at a given angular velocity [70]. From the execution of the test, the peak torque and average peak torque, average power, and total work power will be obtained [70,71,72]. The execution of the test consists of performing a concentric contraction of knee flexion and extension six times [70,72] consecutively and without pause between repetitions at a speed of 60/s and in a range of movement from 0 to 90 degrees, 0 degrees being full extension and 90 degrees being flexion [72]. 

Before the test, 10 squats will be performed as a warm-up. In addition, a familiarization phase with the test will be carried out, in which 10 consecutive repetitions of knee flexion and extension will be performed at a speed of 120/s. Before starting the final test, 1 min of rest time shall be given [73].

Dual-Task Condition

In DT conditions, participants will simultaneously perform the corresponding physical task (strength or balance) and a cognitive task. In this regard, the cognitive task will consist of two-by-two subtractions from a number greater than 100 [74].

Creativity

Firstly, they will be asked to imagine a repetitive situation, and on the other hand, a creative situation [75]: (1) Imagine the reproduction of a model: participants will be asked to imagine themselves reproducing a choreography which has previously shown on a screen (standard and monotonous), and (2) Imagining the performance of a creative task: in the imagined creative task of dance, participants will be asked to perform mentally a free, improvised dance. 

To check that they imagined the requested task, they will have to describe the following aspects verbally after completing the two tasks: (1) imagining reproduction of a model: the color of the room, the elements of the place, the color of the teacher’s clothes, description of movements and a section for them to add further details or observations; (2) imagining the performance of a creative task: the color of the room or place, the elements of the place, description of movements, music or sound, number of stops and a section for them to add further details or observations.

In order to assess brain electrical activity during creative situations, participants will be asked to imagine two different situations with a duration of 3 min each [75].

#### 2.5.3. Secondary Outcomes

##### Sociodemographic Information

Sociodemographic information such as age, level of education, injuries, or falls in the last few months, as well as other health-related information, will be asked.

##### Physical Activity Level

The International Physical Activity Questionnaire (IPAQ) will be used to assess physical activity and inactivity. This has been used to obtain total metabolic equivalents (METs) per week as well as time spent sitting [76]. The Spanish version of the IPAQ [76,77] will be used in this study.

##### Impact of the Disease

Fibromyalgia Impact Questionnaire Revised (FIQ-R)—The FIQ-R [78]—is a self-administered questionnaire consisting of 21 items. Each item is scored from 0 to 10, 10 being the worst condition. It is divided into three domains: (a) function, (b) overall impact, and (c) symptoms, and the maximum score is 100, corresponding to the worst overall symptom impact. The Spanish version of the FIQ-R [79] will be used in this study. This questionnaire will only be administered to people with FM who will participate in this study.

##### Fear of Falling

Falls Efficacy Scale International (FES-I), FES-I, is a self-administered questionnaire that consists of 16 items that are scored on a four-point scale in which the higher the score, the greater the fear of falling [80]. This questionnaire has previously been used in people with FM [81]. The Spanish version of the FES-I will be used in this study [82].

##### Health-Related Quality of Life

EuroQol-5 dimensions-5 levels (EQ-5D-5L) is used to measure health-related quality of life (HRQoL) [83]. It consists of five dimensions (mobility, self-care, activities of daily living, pain or discomfort, and anxiety or depression) and five levels per dimension. The EQ-5D-5L also includes a visual analogue scale (VAS), which rates perceived health status from 0 (worst imaginable health) to 100 (best imaginable health).

##### Sleep Quality

Pittsburgh Sleep Quality Index (PSQI), PSQI, measures the sleep quality and sleep disturbances of the participants over one month on seven components: subjective sleep quality, sleep latency, sleep duration, habitual sleep efficiency, sleep disturbances, use of sleep medication, and daytime dysfunction. Each component is evaluated from 0 to 3, and the total score ranges from 0 to 21 [84]. Higher scores indicate poorer subjective sleep quality. The Spanish version of the PSQI, validated for use in FM patients, will be used [85].

##### Cognitive Impairment

Montreal Cognitive Assessment (MoCA). This brief cognitive screening assesses the following cognitive abilities: attention, concentration, executive functions (including abstraction), memory, language, visual–constructive skills, calculation, and orientation. It has high sensitivity and specificity for detecting mild cognitive impairment even in patients whose performance on the Mini-Mental State Examination (MMSE) is usually in the normal range [86]. It has also been more sensitive than MMSE in people with FM [87]. In addition, 23/30 will be the cut-off point as it has been found to have better diagnostic accuracy, reducing the false positive rate [88]. The administration time required is about ten minutes. The maximum score is 30 [89]. 

##### Sensations Related to tDCS

Survey of sensations related to tDCS. This questionnaire makes it possible to quantify specific subjective feelings and investigate the presence of side or adverse effects of tDCS [90]. A version already published [91] and subsequently modified [92] will be used as a reference. Both versions took into account the effects reported previously [93]. It will be modified, reflecting in each sensation whether it has not been perceived (none) or whether it has been perceived in a mild, moderate, or strong way in each of the sessions received.

##### Anthropometric Measurement 

Body composition will be measured with the Tanita BC-418 Body Composition Analyzer [94]. 

### 2.6. Data Analysis

The outcome results will be included in an anonymous dataset to conduct the statistical analyses. Descriptive and quantitative analyses will be reported. The Statistical Package for the Social Sciences (SPSS, version 24.0; IBM Corp., Armonk, NY, USA) will be employed. Due to the sample size, nonparametric statistical analyses can be the most adequate approach.

In this regard, differences between conditions (1 mA, 2 mA and sham), in all the outcomes, will be analyzed using the Kruskal–Wallis test. Post hoc analyses will be conducted using Mann–Whitney-U tests. Subgroups will be used to study if there are differences in treatment effects according to the presented symptomatology. Furthermore, the [r] effect size will be calculated [95]. Therefore, results will include medians, interquartile ranges, the effect size, and the statistical significance. In order to avoid type I error derived from multiple comparisons, the alpha level of significance will be adjusted according to the Benjamini–Hochberg procedure [96]. 

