## Abstract

People with fibromyalgia could experience physical and cognitive impairments. Furthermore, when performing two tasks at the same time, people with fibromyalgia showed a higher dual-task cost compared to a single task than healthy people. This may result in poorer performance of activities of daily living that are commonly presented as a combination of two or more tasks. Transcranial direct current stimulation (tDCS) is a promising nonpharmacological therapy. However, there is controversy regarding the intensities and the effectiveness of this therapy. Thus, the present study will aim: (1) to compare the effectiveness and the impact of two tDCS intensities (1 mA and 2 mA) on cognitive, motor, brain functions, and cardiac autonomic modulation; (2) to study the impact of tDCS on the dual-task performance and creativity after applying tDCS in dorsolateral prefrontal cortex. In this study, 26 women will participate and will be divided into two groups: women with fibromyalgia (*n* = 13), and healthy controls (*n* = 13). A reduction in cognitive-motor interference in dual-task performance is expected, as well as a modification in neurophysiological parameters and an improvement in cardiac autonomic modulation. Lastly, no different effects are expected depending on the stimulation intensity applied. The obtained results will help to determine if tDCS in the dorsolateral prefrontal cortex could improve the occupational performance of women with fibromyalgia.

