### Hypothesis and Objectives

The hypotheses that are proposed are as follows: (a) the application of tDCS will improve physical performance in physical variables that will be measured through balance and strength tasks; (b) the application of tDCS will improve performance on neurophysiological variables that will be measured through brain electrical activity and HRV; (c) the application of tDCS will improve performance in DT conditions as well as in creativity tasks; (d) tDCS will have different effects depending on the variability of fibromyalgia symptoms presented (pain, sleep problems and depression; (e) no significant effects on the variables would be expected depending on the type of tDCS intensity applied.

At this point, the main objectives of this study are: (1) to compare the effectiveness and the impact of two tDCS intensities (1 mA and 2 mA) on neurophysiological variables, cognitive and motor functions; (2) to study the impact of tDCS on the dual-task performance and creativity after applying tDCS in the dorsolateral prefrontal cortex.

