#### 2.2.2. Recruitment

Taking into account the results of a previous investigation [56], a sample size of 13 achieves 99% power to detect a mean of paired differences of 3.5 with an estimated standard deviation of differences of 2.5 and with a significance level (alpha) of 0.05 using a two-sided Wilcoxon test assuming that the actual distribution is normal. 

Therefore, the sample will be collected during January/February 2022. One group will be composed of women with FM (*n* = 13) from the local association of persons with fibromyalgia, named AFIBROEX, while the other group will be composed of healthy women (*n* = 13).

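### Section 2.6 names no planned test of tDCS against sham: all pairwise comparisons are post hoc to a three-condition test, which fits hypotheses (a)-(c) poorly and gives up some power

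*Protocol article*

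**What the plan says.** The protocol article, under Hypothesis and Objectives, puts the efficacy question in hypotheses (a) to (c). Hypothesis (c), for example, reads "the application of tDCS will improve performance in DT conditions as well as in creativity tasks". The Discussion (section 3) makes sham the comparator for both intensities. Hypothesis (e) then states that "no significant effects on the variables would be expected depending on the type of tDCS intensity applied", and the Discussion repeats that expectation. Objective 1, however, is to compare the two intensities.

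On analysis, section 2.6 says that "differences between conditions (1 mA, 2 mA and sham), in all the outcomes, will be analyzed using the Kruskal–Wallis test". It continues: "Post hoc analyses will be conducted using Mann–Whitney-U tests". Significance is adjusted by the Benjamini-Hochberg (BH) procedure. The section does not say whether the post hoc tests depend on a significant three-way result, or which p-values form the BH family.

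The sample size in section 2.2.2 rests on one paired comparison. It claims that "a sample size of 13 achieves 99% power" when the true paired difference is 3.5 and its SD is 2.5. The test behind this claim is a two-sided Wilcoxon test at alpha 0.05, with normal data assumed.

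**The concern.** The null hypothesis behind (a)-(c) is that active stimulation does not differ from sham. The first test in section 2.6 addresses another null, that all three conditions are equal. It has two degrees of freedom, and one of them goes to 1 mA versus 2 mA, where the protocol expects no difference. A significant three-way result can arise from that contrast alone and then says nothing about (a)-(c). The comparisons that do bear on efficacy come second, as post hoc tests, and they may share their multiplicity adjustment with the intensity comparison.

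At stake are power for moderate effects with 13 women per group, and clarity about which result decides the efficacy claim. The named tests also ignore that each woman contributes all three conditions, whereas the sample size assumed a paired test.

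**Working it through.** **1. The plan's own figure.** Section 2.2.2 gives n = 13, mean paired difference 3.5, SD 2.5, two-sided alpha 0.05.
- Standardised effect: 3.5 / 2.5 = 1.4. Noncentrality: 1.4 × √13 = 5.05.
- Noncentral-t power: 99.6%. With the Wilcoxon efficiency 3/π (13 × 0.955 = 12.4 effective women): 99.4%. Simulated exact signed-rank test: 99.4%.

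The stated 99% reproduces. It belongs to one paired comparison, not to a three-condition test.

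**2. What an omnibus costs in principle.** If both intensities work equally, the pattern (δ, δ, 0) gives a 2-df omnibus and a 1-df pooled active-versus-sham contrast the same noncentrality. Large-sample power, contrast versus omnibus, is 80% versus 71% and 99% versus 98%. A single active-sham pair has 68% where the pooled contrast has 80%. So an omnibus is sensitive to this pattern, though less efficient than a directed contrast.

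**3. What it costs at n = 13 with rank tests.** Simulation of 40,000 runs per row: normal data, no period or carry-over effect, SD of every paired difference 1, both intensities shifted by d, one outcome, alpha 0.05. Success means at least one significant active-versus-sham signed-rank test after BH. The family of three pairs and the Friedman gate are assumptions, not statements in section 2.6.

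| d (SD) | Friedman gate, then BH over 3 pairs | No gate, BH over 3 pairs | Two planned contrasts, BH over 2 |
|---|---|---|---|
| 0 | 2% | 3% | 4% |
| 0.5 | 24% | 32% | 39% |
| 0.7 | 49% | 59% | 67% |
| 0.9 | 73% | 82% | 88% |
| 1.4 (protocol) | 98% | 99.6% | 99.8% |

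- Keeping 1 mA versus 2 mA in the family (column 4 minus column 3) costs 7, 8 and 6 points at 0.5, 0.7 and 0.9 SD. Across repeated runs the range is about 6 to 10 points, with 57-62% versus 65-69% at 0.7 SD.
- A Friedman gate (column 3 minus column 2) adds about 8 to 11 points.
- At 1.4 SD and alpha 0.05 the family cost is 0.2 points.
- If only one intensity works (0.7 SD), three-pair BH gives 49% and the two contrasts 47-48%, so there is no gain.
- If BH across many outcomes lowered the working alpha to an assumed 0.005, the 1.4 SD row would read 81% / 87-88% / 94%.

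**4. A gate with the tests actually named.** With Kruskal-Wallis followed by Mann-Whitney tests and BH over three pairs, gated versus ungated power at 0.7 SD is 63% versus 64% for a within-woman correlation of 0, and 27% versus 28% for a correlation of 0.5. The gate costs about one point.

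**5. The pairing.** The correlation is not in the document, so it is assumed. For a true difference of 2.0 with SD 2.5 (0.8 SD), one paired signed-rank test has 73% power. The Mann-Whitney test has 77%, 48% and 11% at correlations 0, 0.5 and 0.8. Unless the correlation is near zero, this loss is larger than anything in step 3.

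**The case against.** The strongest reply is that a three-condition comparison followed by pairwise tests with multiplicity control is conventional. It also serves objective 1, so 1 mA versus 2 mA is a stated question and not a wasted degree of freedom. That stands, and it is why the intensity comparison should be kept. But it does not supply a named test of (a)-(c).

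A reader might infer that the three-way test decides the trial, and that real tDCS effects are missed when it fails, with a loss of 18 to 26 points. The document does not support this. Section 2.6 states no gate, and its pairwise tests would include both active-versus-sham comparisons. The large figure needs an assumed Friedman gate, which is inefficient with three conditions. It also needs a pooled contrast as benchmark, and that contrast falls to about 25% power at 0.7 SD if only one intensity works. With the named tests a gate costs about one point.

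It is also fair that effects of 0.5 to 0.9 SD are not in the document, whose only stated effect is 1.4 SD. But that effect comes from one previous investigation, and section 2.5.2 lists many EEG, HRV, balance and strength variables as primary. It need not hold for all of them.

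**Conclusion.** The concern holds as a problem of alignment with a modest cost in power. The protocol asks whether tDCS beats sham and expects the intensities to act alike, yet it names no planned active-versus-sham test.

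If BH runs over all three pairs within an outcome, the loss is about 6 to 10 points for effects of 0.5 to 0.9 SD. This assumes paired tests, 13 women, normal data and both intensities working equally. The loss nearly vanishes at 1.4 SD with alpha 0.05, and is nil if only one intensity works. A further 8 to 11 points would be lost only under a Friedman-type gate, which the article does not state. It would go too far to say that real effects are generally missed.

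The independent-samples tests in the same two sentences are the graver fault. Replacing them with Friedman and signed-rank tests would not by itself cure the misalignment. Severity: minor to moderate, a cheap improvement.

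**What to change.** In section 2.6:
- Name 1 mA versus sham and 2 mA versus sham as the planned within-woman tests of hypotheses (a)-(c), for example by Wilcoxon signed-rank test.
- Enter these p-values in the Benjamini-Hochberg procedure directly, say which p-values form that family, and state that the tests do not depend on an omnibus result.
- Report 1 mA versus 2 mA as a separate paired analysis for objective 1 and hypothesis (e).
- If wanted, report the mean of the two active conditions minus sham as supportive only, because it is diluted when one intensity does not work.

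The cost is wording: no new data or participants. In the simulation the chance of a false active-versus-sham finding with no true effect stays at about 4%. The downsides are that no single three-way p-value is reported, and that the intensity comparison sits in its own family.

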## 2. Materials and Methods

### 2.1. Study Design

This study is a double-blind, sham-controlled, crossover study. All participants will randomly participate through all conditions (1 mA, 2 mA, and sham). This study, in order to fulfil correctly the items of the standard protocol for clinical trials, has followed the SPIRIT 2013 Statement Items [55].

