### 2.4. Intervention

The transcranial direct current stimulation (tDCS) will be conducted with an 8-channel hybrid EEG/tDCS wireless neurostimulator (Starstim, NEuroelectrics, Barcelona, Spain). The electrodes used will be sponge electrodes (Sponstim^®^, 5.65 cm de diameter, 25 cm^2^ surface area) soaked in saline solution. 

Since the DT involves the prefrontal cortex in the main role [23], the active electrode will be placed on the left prefrontal cortex, corresponding to the F3 region of the international 10–20 electrode placement system. The return electrode will be placed on the contralateral supraorbital region (Fp2) [27,44,45,46,48,49,57,58]. At the same time, the HRV and EEG signals will be recorded at Cz, C4, P3, P4, and Oz. Patients will receive tDCS at an intensity of 1 mA (Condition 1) or 2 mA (Condition 2) for 20 min, with a ramp up and ramp down of 30 s each. A duration of 20 min will be applied to ensure that the acute effects remain for at least 1 h [30]. For the placebo or sham condition (Condition 3), the mode included in the NEuroelectrics NIC1 program will be used, consisting of a double sham with a 30 s double ramp up and ramp down. These parameters for Condition 3 were chosen based on previous reports of perceived skin sensations, which generally disappear within the first 30 s [59,60]. 

There will be a minimum of seven days between conditions. One stimulation session will be applied each week. A different stimulation will be applied each week. In total, three weeks are estimated for each participant to complete the study. The intervention and all assessments will be carried out at the Faculty of Sport Sciences (Caceres, Spain).

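### The three conditions are measured in the same women, but section 2.6 compares them with tests for independent samples, so the 99% power computed for a paired test need not hold

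*Protocol article*

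**What the plan says.** Section 2.1 fixes the design: "This study is a double-blind, sham-controlled, crossover study". It adds: "All participants will randomly participate through all conditions (1 mA, 2 mA, and sham"). Section 2.4 spaces the sessions: "There will be a minimum of seven days between conditions". Each woman is expected to finish in three weeks, with a different stimulation each week. Every outcome therefore gives three related results per woman.

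Section 2.2.2 sizes the study on that basis. It states that "a sample size of 13 achieves 99% power to detect a mean of paired differences of 3.5". The SD of those differences is put at 2.5, and the calculation is made "using a two-sided Wilcoxon test assuming that the actual distribution is normal". This is a one-sample calculation on within-woman differences, that is, a signed-rank test.

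Section 2.6 prefers nonparametric methods because the sample is small. It then states, for all outcomes, that differences between the three conditions "will be analyzed using the Kruskal–Wallis test. Post hoc analyses will be conducted using Mann–Whitney-U tests". It names no related-samples test and no model with a participant effect.

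**The concern.** Kruskal–Wallis and Mann–Whitney tests judge the difference between conditions against the full spread of results, including stable differences between women. A crossover removes that component by comparing each woman with herself. If the component is large, the planned tests set the effect against noise that the design has already eliminated.

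The choice affects every condition comparison in every outcome, including main objective 1, the comparison of 1 mA with 2 mA. Hypothesis (e) expects no significant effect of intensity. An insensitive test makes that expected result easier to obtain, whether or not the intensities differ.

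**Working it through.** **Inputs.** From section 2.2.2: n = 13, mean paired difference 3.5, SD of differences 2.5, two-sided alpha 0.05. From section 2.1: three conditions per woman. Assumed, because the documents do not say: one group of 13 analysed on its own, normal data, equal correlation rho between any two of a woman's results, and both active conditions shifted equally against sham.

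**Step 1: reproduce the plan's figure.** The standardised paired effect is 3.5 / 2.5 = 1.4. The noncentrality of the paired t-test is 1.4 × √13 = 5.05, which gives power 99.6%. With the Wilcoxon efficiency factor 3/π, the effective n is 13 × 3/π = 12.4 and power is 99.4%. Simulating the exact signed-rank test (critical value 17, size 0.048) also gives 99.4%. The stated 99% is right for the paired test.

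**Step 2: what an unpaired test sees.** The SD of differences satisfies SD_d² = 2σ²(1 − rho), so the SD within one condition is σ = 2.5 / √(2(1 − rho)). For example, at rho = 0.7, σ = 2.5 / √0.6 = 3.23, and the unpaired standardised effect is 3.5 / 3.23 = 1.08. An independent-samples test works as if the variance of a difference were 2σ², when it is 2σ²(1 − rho). That is why it becomes conservative as rho rises.

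**Step 3: simulate all the tests on the same data** (40,000 trials per setting, nominal alpha 0.05, no multiplicity adjustment).

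| rho | σ | 3.5/σ | Kruskal–Wallis power | Mann–Whitney power (active vs sham) | Kruskal–Wallis null rejection |
|---|---|---|---|---|---|
| 0 | 1.77 | 1.98 | 99.9% | 99.6% | 4.7% |
| 0.3 | 2.11 | 1.66 | 99.4% | 98.7% | 1.6% |
| 0.5 | 2.50 | 1.40 | 96.9% | 95.8% | 0.5% |
| 0.7 | 3.23 | 1.08 | 81.6% | 82.3% | 0.06% |
| 0.8 | 3.95 | 0.89 | 55.4% | 60.4% | 0.02% |
| 0.9 | 5.59 | 0.63 | 13.8% | 19.9% | <0.01% |

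The matched tests do not depend on rho here, because the SD of differences is held at 2.5. Friedman power is about 98.6% and signed-rank power about 99.4% throughout, and both reject a true null about 5% of the time. Repeat runs move Kruskal–Wallis power by up to about one percentage point. They put its null rejection at 1.6 to 1.8% for rho = 0.3 and 0.06 to 0.08% for rho = 0.7.

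**Step 4: a smaller effect.** For an assumed difference of 2.0, Kruskal–Wallis power is about 62 to 63% at rho = 0.3, 43% at 0.5 and 16 to 17% at 0.7, against about 66% for Friedman. Mann–Whitney power is 61%, 45% and 22%, against 73% for signed-rank.

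**The case against.** **The harm depends on an unknown correlation.** This stands. At the planned effect nothing meaningful is lost at rho of 0.3 or below, and at 0.5 the loss is small. At rho = 0.2 Kruskal–Wallis is slightly ahead of Friedman (99.7% against 98.5%; for a difference of 2.0, 69% against 65%). Null rejection is 3.6% at rho = 0.1 and 2.2% at 0.2. A reader might infer that any positive correlation makes the tests far too conservative, or that real effects will certainly be missed. The documents support neither reading.

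**The correlation may be low.** Section 2.5.1 measures the tasks before and after stimulation in each session, and section 2.6 does not say whether post values or changes are compared. Change scores would remove much of the stable variation between women, so the figures at 0.8 and 0.9 may not apply. But three changes from one woman are still not independent samples.

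**Mann–Whitney may be meant for fibromyalgia against healthy women.** It would suit that comparison. Section 2.6, however, names it as the post hoc test to the Kruskal–Wallis comparison of conditions.

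**An article condenses a fuller plan.** That covers omissions. Here the article names specific tests, and they do not fit its own design.

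**Conclusion.** The analysis is wrong as written. Design and sample size are paired, while the named tests are unpaired. The stated 99% power belongs to the paired test and need not carry over. The loss at the planned effect is serious from a correlation of about 0.7 upward; for a difference of 2.0 it is already material at 0.5. These sizes rest on the assumptions listed in the working. In particular, analysis within one group of 13 is assumed, because section 2.6 does not say whether the two groups are pooled. The Benjamini–Hochberg adjustment would lower power further for any of the tests.

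Two stronger readings should be resisted. First, a reader might infer that significant results from the planned tests could not be trusted. At zero or positive correlation the null rejection rate stays at or below 5%, so false positives are not inflated; the risk is of missed effects. Second, a reader might take the figures as measuring the bias in the 1 mA against 2 mA comparison. Both active conditions were shifted equally, so no intensity difference was simulated. Only the direction, towards a non-significant result, is established.

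**What to change.** In section 2.6, compare the three conditions within each group with the Friedman test, followed by Wilcoxon signed-rank tests on the within-woman pairs, and compute r from the signed-rank Z. This keeps the nonparametric approach and agrees with section 2.2.2.

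A linear mixed model, with woman as a random effect and condition and period as fixed effects, is an alternative. It is not equivalent: it is parametric, adjusts for period and estimates a different quantity, and r from a signed-rank Z would not come from it.

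Mann–Whitney may stay for comparing women with fibromyalgia with healthy women, provided the text limits it to that use.

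The cost is two sentences of wording. No new data are needed, and SPSS offers these procedures.

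### The general rule of medians, interquartile ranges and Benjamini–Hochberg-adjusted tests also covers the tDCS sensations survey, where it could hide strong sensations felt by a minority of women

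*Protocol article*

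**What the plan says.** The sensations survey stands under 2.5.3 Secondary Outcomes. Its stated purpose includes detecting side or adverse effects. Each sensation is recorded as "whether it has not been perceived (none) or whether it has been perceived in a mild, moderate, or strong way in each of the sessions", so the data are ordinal with four levels, one score per sensation and session.

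Section 2.6 sends differences between sham, 1 mA and 2 mA, for all outcomes, to a Kruskal–Wallis test with Mann–Whitney post hoc tests. On reporting it says: "Therefore, results will include medians, interquartile ranges, the effect size, and the statistical significance". On multiplicity it says: "In order to avoid type I error derived from multiple comparisons, the alpha level of significance will be adjusted according to the Benjamini–Hochberg procedure". It names no exception for the sensations survey, mentions no counts by severity, and does not say which tests form the adjustment family. It also says, in general terms, that descriptive analyses will be reported.

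On numbers, the abstract says "26 women will participate and will be divided into two groups", and 2.2.2 gives 13 per group. Under 2.1 every woman receives all three conditions.

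**The concern.** Medians and quartiles describe the middle of a distribution. Adverse sensations matter at its upper end, and often only a minority report them. When at least about three quarters of the women report none, all three quartiles are *none* however severe the remaining reports are.

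The multiplicity adjustment adds a second problem. It guards against false claims of benefit across many EEG, HRV, balance and strength outcomes. For a harm, the same guard raises the bar for noticing it, and raises it further as more unrelated outcomes enter the family.

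At stake is the tolerability comparison of the three conditions. A table row that reads *none (none–none)* and not significant for both active intensities could conceal reactions that a simple count would show.

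**Working it through.** **The plan's own figure.** The only calculated figure in the article is the 99% power in 2.2.2 (n = 13, mean paired difference 3.5, SD 2.5, two-sided alpha 0.05, Wilcoxon). It reproduces: 99.6% by the noncentral t and 99.4% by simulating the exact signed-rank test. It has no bearing on tolerability.

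**Inputs.** n = 13 per group or 26 pooled, in each of three conditions (abstract, 2.1, 2.2.2). Levels are coded none = 0 to strong = 3. Assumption: k women score 3 in one condition, and all other scores are 0.

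**Step 1: quartiles.** By the (n + 1)p definition, the upper quartile lies at rank 0.75 × 14 = 10.5 for n = 13 and 0.75 × 27 = 20.25 for n = 26. By linear interpolation it lies at 1 + 0.75 × 12 = 10 and 1 + 0.75 × 25 = 19.75.

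| Strong / n | Share | Q1, median | Q3, (n + 1)p | Q3, linear |
|---|---|---|---|---|
| 2/13 | 15.4% | 0, 0 | 0 | 0 |
| 3/13 | 23.1% | 0, 0 | 1.5 | 0 |
| 4/26 | 15.4% | 0, 0 | 0 | 0 |
| 5/26 | 19.2% | 0, 0 | 0 | 0 |
| 6/26 | 23.1% | 0, 0 | 0.75 | 0 |

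The median alone stays at *none* up to 6/13 or 12/26 (46%).

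**Step 2: the planned tests, unadjusted.** For k strong scores in one condition and none in the other two, the tie-corrected Kruskal–Wallis statistic reduces to H = 2k(N − 1)/(N − k), with N the total number of scores. On 2 degrees of freedom, p = exp(−H/2).
- 2/13 v 0 v 0: N = 39, H = 4 × 38/37 = 4.11, p = 0.128.
- 4/26 v 0 v 0: N = 78, H = 8 × 77/74 = 8.32, p = 0.016.
- 5/26 v 0 v 0: N = 78, H = 10 × 77/73 = 10.55, p = 0.005.

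If the other conditions are not empty, the pooled signal weakens: 4/1/0 of 26 gives p = 0.064, 4/2/0 gives 0.118 and 4/1/1 gives 0.201.

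For Mann–Whitney, k v 0 gives z² = k(N − 1)/(N − k), now with N over two conditions:
- 2/13: z = 1.44, p = 0.149.
- 4/26: z = 2.06, p = 0.039.
- 5/26: z = 2.33, p = 0.020.

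The effect size r = z/√N is 1.44/√26 = 0.28, 2.06/√52 = 0.29 and 2.33/√52 = 0.32.

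**Step 3: Benjamini–Hochberg.** The i-th smallest of m p-values is compared with 0.05i/m.
- p = 0.016 (0.0156 unrounded), if it is the smallest, survives with m = 3 (0.05/3 = 0.0167) and fails with m = 4 (0.05/4 = 0.0125). In a larger family it needs about 0.0156/0.05 = 31% of the tests to be rejected.
- p = 0.005 (0.0051 unrounded) needs at least 6 of 50, or 11 of 100, p-values that small.
- Within three pairwise comparisons of one sensation, 0.039 becomes 0.039 × 3/2 = 0.059 and 0.020 becomes 0.030.

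The article does not give m. As an illustration, 19 EEG channels × 6 bands (2.5.2) would give 114 tests for one recording if each were tested. The five recording sites named in 2.4 would give 30.

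**Step 4: what counts would show.** 2/13 is 15.4% (exact 95% CI 1.9% to 45.4%). 4/26 is 15.4% (4.4% to 34.9%).

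**The case against.** The strongest reply is that this concerns something left unsaid. The list of results is introduced as what they will include, not as all they will contain, and descriptive analyses are promised. A severity table is the kind of detail that a condensed article may leave to a fuller document. That stands as far as it goes: counts are not excluded. But the article does more than stay silent. It states a rule, gives it the scope of all outcomes, and the rule does not suit this one.

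A second reply is that the scope wording is loose, since the secondary-outcome heading also covers age, education and body composition, for which a test between stimulation conditions makes no sense. That is true. The sensations survey, however, is collected after each stimulation session and is a natural candidate for such a test, so the loose wording does reach it.

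Third, the planned effect size r, at about 0.3 in these examples, would still signal a difference. This also stands. It softens the loss of information but does not tell a reader how many women had a strong sensation.

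Fourth, the data pattern is a chosen one. If more than half of the women felt something mild, the median would be *mild*. That is correct, though such a median would still not show the strong reports.

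**Conclusion.** The point holds as a mismatch between a stated rule and one outcome. Under 2.6 as written, strong sensations in 2/13 or 4/26 women could be summarised as *none (none–none)*. Significance could also be lost, depending on the undefined adjustment family. Within one group of 13, the 2 v 0 v 0 pattern is non-significant before any adjustment (p = 0.128), and the cause there is sample size, not Benjamini–Hochberg. The results rest on 0–3 coding and on all other women reporting none; the 15% rate is an illustration, not a figure from the article.

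A reader might infer that strong sensations will be reported as absent and non-significant. The article does not support that: counts remain possible, r would be reported, and the pooled 4/26 and 5/26 patterns are nominally significant (p = 0.016 and 0.005). A reader might also infer that a stated aim is compromised. The objectives compare the intensities on neurophysiological, cognitive and motor measures. Tolerability is not among them, and nothing says that non-significance will be taken as equal tolerability.

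**What to change.** In 2.6, add a short paragraph on the sensations survey:

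- Exclude it from the Benjamini–Hochberg family.
- For each sensation, each condition (sham, 1 mA, 2 mA) and each group (fibromyalgia, healthy), report the number and percentage of women at each severity level.
- Report within-woman (paired) differences between conditions with 95% confidence intervals, since every woman receives all three.
- State that a non-significant difference will not be read as equal tolerability.

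The cost is one paragraph and one extra table; the data are already collected. The intervals will be wide at these sample sizes, and unadjusted comparisons of harms may give some false signals. The paragraph should say so.
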